### Sample size

We estimated that the intervention would be relevant if it provided an 8 % absolute increase in the colorectal cancer screening participation rate (22 % in the control group and 30 % in the intervention group). With a two-sided α risk of 0.05 and a β risk of 0.1, and assuming an intraclass correlation coefficient for clusters of 0.004 and a mean of 500 patients per cluster (assuming an average of 2000 people per IRIS zone and percentage of people between 50 and 75 years equal to 25 % of the total population), we needed 4 clusters per group (2000 people per group). Taking into account the three groups (one intervention group and two control groups) and stratified by department gives a total number included about 30 000 individuals.

We establish that the number of IRIS zones needed to meet the objectives of the study is 20 intervention IRIS zones and 40 control IRIS zones [24].

So, for each district, we will randomly select:four contiguous intervention IRIS zoneseight control IRIS zones divided into two groups (one adjacent and one distant from the intervention group)

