**Fig. 1 Fig1:**
[figure not shown]
Conceptual model of patient navigation (Fiscella 2011)

The main role of the navigators is to promote CRC screening among the target population to increase participation rates in these areas. The missions of the navigators are to contact individuals living in the intervention area and invited by the screening structure and to guide them to the realization of the screening test.

Navigators’ activities will be: 1) to establish partnerships with local associations, religious places, health centers, health fairs, GPs… in order to participate in local events and to meet the target population 2) to find a committee room to meet people who are in need 3) to communicate by phone or face-to-face with the target population 4) to provide personalized assistance to each person in order to help them to overcome obstacles in the realization of the screening test (psychological, financial or logistical barriers) 5) to collect patient socio-demographic information.

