### Outcomes assessments

#### Primary outcome

To assess the effectiveness of the intervention, the primary outcome will be measured by the difference between before/after participation rates in the intervention zones and in the control zones. Other criteria will be used according to the recommendations made by the National Patient Navigation Leadership Summit (NPNLS) and published in Cancer in 2011 [29]: time to participate, participation in the whole procedure, time to complete the colonoscopy after a positive FOBT test result.

Eighteen months after the beginning of the intervention, each screening management structure, in charge of sending the invitation to individuals included in the mass screening program, will collect the participation status of the men and women included in the study. Each district structure has a database with the contact details of all individuals, eligible to receive an invitation to the national screening program. After the beginning of the intervention, the 18 month-participation rates will be measured, in selected areas. The following items will be measured: program coverage rate (percentage of people guided by navigators), screening participation rate, percentage of patients who get screened after the navigator intervention, colonoscopy completion rate.

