### Statistical analysis

#### Quantitative analysis

All collected individual variables will be described by frequency (%) for categorical variables, and mean (SD) and median (Q1 -Q3) for quantitative variables. The data will be summarized separately in two tables: one for the period before intervention, and another for the period after intervention. The effectiveness of the intervention will be measured comparing the delta of before-after participation rate in intervention area and control areas. Completion time of the exams (screening test and colonoscopy) between intervention areas and control areas before and after the intervention will also be compared. The difference in participation will be analyzed by logistic regression analysis methods taking into account the interactions between the period and area. The influence of other collected variables will be tested using univariate tests (Chi2 or Fisher test for categorical variables and Student or Wilcoxon test for quantitative variables). A multivariate model will be implemented in order to take possible confounding factors into account. Analysis of participation time will be done in two ways: firstly by taking the censored data with a Cox model into account and secondly with a ANOVA model (on the subgroup of patients who participate). The level of statistical significance will be of 5 %.

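### The participants-only ANOVA of participation time does not compare the allocated groups, and the direction of its bias is unknown; it should be descriptive, with inference resting on all invited people

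*Protocol article*

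**What the plan says.** The Quantitative analysis section of the Protocol article plans a pair of analyses for this time measure. One keeps people who have not taken part as censored observations, using a Cox model. The other is restricted to a subgroup: "secondly with a ANOVA model (on the subgroup of patients who participate". The same section sets the contrast of interest for times: "Completion time of the exams (screening test and colonoscopy) between intervention areas and control areas before and after the intervention will also be compared". It closes with a single 5% significance level for the analyses. Nothing there limits the ANOVA to description.

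Under Primary outcome, the primary measure is the before/after difference in participation rates. Time to participate belongs to a list of further criteria: "time to participate, participation in the whole procedure, time to complete the colonoscopy after a positive FOBT test result".

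Two other statements matter. The text below Fig. 1 gives the navigators' main role as to "promote CRC screening among the target population to increase participation rates in these areas". The Sample size section plans for "22 % in the control group and 30 % in the intervention group".

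**The concern.** Whether a person participates is settled after randomization, and raising participation is the purpose of the intervention. A subgroup defined by participating is therefore partly a product of navigation. In the control zones it holds people who take part under the usual invitation. In the intervention zones it holds those people plus anyone who took part only because of the navigator. A difference in mean time between these two sets mixes any real change in timing with a change in who is being timed, and randomization does not protect the comparison.

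At stake is the reading of the time result. The ANOVA could report that navigation slows or speeds participation when no individual's timing has changed. It could also show nothing while navigation brings in more people. Either result could sit beside a Cox analysis that says something different about the same question.

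**Working it through.** **1. Planning rates.** The plan states no figure for the time analysis, so the check starts from its participation rates, once these are confirmed as the basis of the stated sample size.
- Inputs from Sample size: "22 % in the control group and 30 % in the intervention group"; "With a two-sided α risk of 0.05 and a β risk of 0.1"; "intraclass correlation coefficient for clusters of 0.004 and a mean of 500 patients per cluster".
- Two-proportion formula: 630 per group without continuity correction, 655 with it.
- Design effect: 1 + (500 − 1) × 0.004 = 2.996.
- Inflated size: 630 × 2.996 = 1,887, or 655 × 2.996 = 1,962.
- Clusters: 1,887/500 = 3.77, or 1,962/500 = 3.92. Both round up to 4 clusters, or 2,000 people, per group, as stated.
- Total: 5 districts × 3 groups × 4 zones × 500 = 30,000, as stated.

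The stated sample size reproduces, so 22% and 30% are the plan's working rates.

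**2. Composition of the participant subgroup.** Assume that navigation only adds participants, so that the 22% who would take part anyway still do so. Of every 100 invited people in an intervention zone, 22 are usual participants and 30 − 22 = 8 are added. The share of intervention-zone participants with no control counterpart is 8/30 = 26.7%.

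**3. Spurious difference.** Let m be the mean time of usual participants, the same in both arms, and m + d the mean time of added participants. No individual's timing changes.
- Control mean among participants: m.
- Intervention mean among participants: [22m + 8(m + d)]/30 = m + (8/30)d.
- Difference: (8/30)d.

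The documents do not give d, so a range is assumed:

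| Added minus usual participants, d (months, assumed) | Apparent difference in mean time (months) |
|---|---|
| −3 | −0.8 |
| 0 | 0 |
| +3 | +0.8 |
| +6 | +1.6 |
| +9 | +2.4 |

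The sign follows d. A positive d looks like delay and a negative d looks like speeding up, although nobody was slowed or speeded.

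**4. Before/after contrast.** Suppose the participants' mean time is m in both areas before the intervention and stays m in the control zones afterwards. The contrast of changes is then [m + (8/30)d − m] − [m − m] = (8/30)d. The shift in composition arises only in the intervention zones in the after period, so the contrast does not remove it.

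**5. Can it contradict the Cox model?** A simulation used 10,000 people per arm (20 zones × 500), follow-up to 18 months, and usual participants uniform over 0–12 months (assumed). It treated individuals as independent, so its p-values are illustrative only.
- Added participants uniform over 6–18 months: participants' means are 5.99 (control) and 7.65 (intervention) months, so the ANOVA says slower (p < 0.001). The Cox hazard ratio in everyone is 1.36, towards more or earlier participation.
- Same, but usual participants in the intervention arm made 10% faster: the ANOVA still shows 1.23 months slower, and the Cox hazard ratio is 1.38.
- Added participants timed like the others (0–12 months): the ANOVA difference is 0.03 month, p = 0.79, while the Cox hazard ratio is 1.40.

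The two analyses can therefore point in opposite directions, or one can show nothing where the other shows an effect.

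**The case against.** The strongest reply is about consequence. Time to participate is not the primary measure, the Cox model that keeps censored people is already planned and is listed first, and a reader would see the ANOVA beside it. Time among participants is also a legitimate description. All of this stands. It limits the weight of the point and means that the participants-only figures need not be removed. It does not make a between-group test on that subgroup valid.

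Three stronger readings are tempting, and the documents do not support them.
- **Navigation will appear to slow participation.** A reader might infer this by supposing that people brought in by a navigator are late, hard-to-reach responders. No section gives a distribution of participation times or says whether navigated people come earlier or later. With equal timing the spurious difference is zero, and with earlier timing it reverses. For the same reason, a large test statistic computed from one assumed set of means and standard deviation would say nothing about this trial.
- **The ANOVA ignores clustering.** The article does not say how clustering enters any of its models. A condensed article commonly leaves that to the full protocol or analysis plan, so this silence is not a fault of the ANOVA.
- **The plan gives no order between the two analyses.** It does list the Cox model first and the ANOVA second. That is an order, though not a statement that the second is descriptive only.

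**Conclusion.** The point holds in a limited form. The ANOVA of participation time among participants selects on an outcome that the intervention is designed to change, so it is not a comparison of the allocated groups, and the before/after contrast does not repair it. At the plan's rates, 27% of intervention-zone participants would have no control counterpart. This rests on the assumption that navigation only adds participants. If nobody's own timing changes, the bias is (8/30) × d: 0 to 2.4 months for d between 0 and 9 months, and of opposite sign for negative d. The values of d are assumed, so the direction and size in this trial are unknown.

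A reader might infer that the trial's conclusion on effectiveness is threatened. It is not: that conclusion rests on participation rates among all eligible people in the zones, and the point touches only the interpretation of a non-primary time measure.

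**What to change.** In the Quantitative analysis section, state that inference about participation time rests on all invited people, through the Cox model already planned or through cumulative participation over time since invitation. State that times among participants will be reported by group and period as description only, without a between-group test and without a causal reading. If cumulative participation is chosen, the time points are the study team's choice and should be set in advance.

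The change is to wording. No data collection, sample size or conduct is affected. The cost is the loss of one supportive test.

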#### Qualitative analysis

First, recorded interviews will be transcribed in verbatim. Transcripts will be read holistically, and then line-by-line to extract significant statements from the interviews, following established guidelines for a thematic analysis. These statements will be used to generate specific codes, and each transcript will then be coded using this thematic coding scheme. The themes emerging from the first interviews will help to refine the interview guide used for the next set of interviews. The latter will in turn be used to inform the next set and so on. Data analysis will be performed simultaneously and continually with the data collection, in order to identify the arising of data saturation. The gathered information will then be categorized into five main themes, based on the objectives of the study.

#### Cost effectiveness analysis

In order to estimate the cost-effectiveness of the implementation of such a program, marginal costs, with encryption on the actual cost, observed during the installation, as well as a projection on a routine cost will be taken into account.

#### Organizational analysis

The content of the interviews with navigators and institutional partners will be subject for a qualitative analysis by the IRaMuTeQ software. A statistical analysis of different texts will be performed in order to generally describe the corpus (number of texts, occurrences, of forms …). This will determine the navigators’profiles, as well as a hierarchical organizational structure. It will also create a theoretical model for action.

## Discussion

This study aims: 1) to implement a PN intervention for which the efficacy has been demonstrated in a different context 2) to assess the effectiveness of the intervention in this context 3) to identify the context characteristics that may interact with the effect of the intervention (factors favoring or hindering). The ColoNav project should make it possible to determine if the patient navigation program is suitable and if it works in the context of the French healthcare system. It should allow us to identify the effects of the context and to give details concerning the specific favoring and hindering factors. Finally, ColoNav will allow the creation of a new enhanced program. If this intervention is estimated as being cost effective, it could create new dynamics for peer approaches. The latter could be developed for the screening program of other cancers or other chronic diseases.

## Abbreviations

CRC, colorectal cancer; EDI, European Deprivation Index; FOBT, fecal occult blood test; GP, general practitioner; INCA, Institut National du Cancer; NPNLS, National Patient Navigation Leadership Summit; PN, patient navigation; PROWG, Patient-Reported Outcomes Working Group
